## Interventions

### Explanation for the choice of comparators

Participants on the control arm will receive routine practice. The results from a PHE survey [15] and a PSP on the oral health of older adults [16] suggest that this practice is likely to be heterogeneous and include intermittent tooth brushing with toothpaste by the residents, who usually rely on support from the care home staff for their oral hygiene. This has been confirmed by a review of existing literature on oral health practices in care homes [22], as well as preliminary qualitative research findings from a recent project carried out in care homes in North London (unpublished). The process evaluation will enable the research team to gather information about current practice in care homes assigned to the control arm. Furthermore, collecting information on the control group’s willingness to be randomised to the control arm, as well as follow-up and response rates will help inform and plan for a future larger scale definitive trial.

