A care home staff training package (containing a training video and hard copy training manuals and laminated reference guides, as well as online training through a dedicated website as described above) to facilitate appropriate knowledge and skills to implement oral health promotion activities. Care home staff will be required to undertake formal training to support the residents’ oral health prior to the residents completing the baseline assessments. The training will be overseen by the care home manager and the research team, and will be added to the log of mandatory training. Following the initial training prior to baseline assessments, care home staff will have access to the training package online at anytime during the study. The turnover rate of employed staff working in the UK care sector is high; it is therefore probable that a change in care staff involved in the study will occur. As a result of this, the training package will also be part of the induction training for new staff members.Administration by trained care home staff of OHAT, a brief and practical assessment of the resident’s oral health needs that is reviewed and updated over time. Administration will take place immediately prior to the initial dental assessment at baseline and at the 12-month follow-up visit. Care home staff will also be asked to complete a ‘Personal Oral Care Plan’ for each resident following completion of the OHAT, and will be asked to update it after reassessment of the OHAT or after any dental visit.A ‘support worker assisted’ daily tooth-brushing regime with toothpaste containing 1500 ppm fluoride (provided by the study). This will involve care home staff brushing the teeth of residents who have problems with their oral self-care or providing assistance to those residents who are able to brush their own teeth. This may include reminders to brush their teeth as well as guidance on brushing appropriately. Tooth brushing will be undertaken twice daily, once in the morning and once in the evening. To facilitate this, a guide on how to deliver oral care will be provided in the form of a poster and ‘Tips and Tricks’ cards. These ‘Tips and Tricks’ cards are relevant to residents who can brush their own teeth, who require assistance or who might refuse care. Care home staff will be asked to record daily tooth brushing on the ‘Weekly Oral Hygiene Record’ along with any ‘Tips or Tricks’ they used. The record will be used to assess fidelity of the intervention implementation.

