### Outcomes

This study does not have a primary outcome measure. The main aim of this study is to determine the feasibility of a multi-centre cluster-randomised trial for the prevention of oral disease in older people in care homes. The feasibility study will provide necessary information to enable selection of the most appropriate primary outcome measure, estimates of treatment effects and other important parameters to plan for a definitive trial. The outcome measures that will be recorded in this study are as follows:
Clinical outcomes (assessed at baseline and 12 months by a dental examiner) will include the number of teeth, number of teeth with coronal and root caries lesions, the proportion of teeth with visible plaque and the proportion of teeth that bleed on probing;Oral symptoms and urgent dental care refers to the number of reported episodes of dental pain, sepsis, discomfort and urgent dental care appointments (collected weekly by care home staff and at baseline, 6 and 12 months by researchers);Health-related quality of life using the EuroQol five dimensions questionnaire – EQ-5D5L [27] (collected at baseline, 6 and 12 months);Oral health-related quality of life using the Oral Impacts on Daily Performances (OIDP) [28] (collected at baseline, 6 and 12 months); andOral health needs assessed by OHAT [26] (collected by dental examiners at baseline and 12 months).

The EQ-5D is the most commonly used outcome in health economics evaluation studies to calculate QALYs, preferred also by NICE [29]. Its responsiveness has not been proven for oral conditions and therefore the additional use of condition-specific measures is recommended [30]. The OIDP is a brief and widely used oral health-related quality of life outcome measure, validated also amongst older adults in the UK [28]. It is included in the national dental health surveys of adults in the UK [31] and previously used in care homes in London in an interviewer-administered format to provide self-reports of residents about the impact of oral conditions on key aspects of their daily life, such as eating, speaking, cleaning teeth, smiling, relaxing, and enjoying the contact of other people [2].

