Data will be collected to facilitate the assessment of the fidelity of the intervention. This refers only to the care homes in the intervention arm of the study and will include information on completion rates (fully, partially or not completed) for the following: (1) OHAT administered by trained care staff to participants; (2) Personal Care Plan for participants; (3) Weekly Oral Hygiene Record of participants; (4) Care Staff Completed Training.

As part of the process evaluation, semi-structured interviews with care home staff (managers, carers and other staff) and residents will assess the intervention’s feasibility (issues relating to recruitment, retention and fidelity) and acceptability. How the intervention could be embedded in standard practice will also be explored using the different domains of Pfadenhauer et al.’s [21] framework (Table 1). Specifically, the framework will be used to determine the factors that are important for implementation.

**Table 1 Tab1:** Domains and questions for reflection from Pfadenhauer et al. [21]

Main	Questions for reflection
Intervention characteristics	Which intervention characteristics interact with the setting, the context and the implementation? How do these intervention characteristics interact with the setting, the context and the implementation?
Context	How do aspects of the context interact with the intervention? Which aspects of the context interact with the implementation of the intervention?
Implementation theory	Which theoretical underpinning guides the implementation? How does this theory interact with the setting and the context? How does it interact with the intervention?
Implementation process	Which stages of the implementation process are passed through during implementation? How does the implementation process interact with the setting and the context? How does it interact with the intervention?
Implementation strategy	Which strategies are employed during implementation? How do these implementation strategies interact with the setting and the context? How do they interact with the intervention?
Implementation agents	Which agents are involved in the implementation effort? How do these implementation agents interact with the setting and context? How do they interact with the intervention?
Implementation outcomes	Which implementation outcomes are reported with the setting and the context? How do these implementation outcomes interact with the intervention outcomes?

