## Data collection and management

### Plans for assessment and collection of outcomes

#### Feasibility study

All study participants (intervention and control arms) will undergo an oral examination to collect clinical data. Participants will also provide self-report information on person-centred measures via interviewer-administered validated questionnaires and a symptom checklist. The following assessments will take place at the care home for each selected resident:

• Clinical outcomes will include the number of teeth, number of teeth with coronal and root caries lesions, the proportion of teeth with visible plaque and the proportion of teeth that bleed on probing. The dental examination will be undertaken at baseline and at 12 months by trained dental examiners, commissioned by the research team from the South Eastern HSC Trust, in Northern Ireland, and the Whittington Health Dental Services, in North London.

• A brief and practical assessment of the resident’s oral health needs. This will be assessed using the OHAT questionnaire [26]. The dental examiner will undertake this assessment at baseline and 12 months.

• Oral symptoms and urgent dental care: This refers to the number of reported episodes of dental pain, sepsis, discomfort and urgent dental care appointments. Care support staff using a checklist diary log will collect this information weekly. Research assistants will also collect this information at baseline, 6 months and 12 months.

• Health-related quality of life will be assessed through the EQ-5D-5L questionnaire [27]. This questionnaire will be administered by a trained research assistant to all participants at baseline, 6 and 12 months.

• Oral health-related quality of life will be assessed using the OIDP questionnaire [28]. This questionnaire will be administered by a trained research assistant to all participants at baseline, 6 and 12 months.

In addition, data will be collected at care home level (from the care home managers) for all participating care homes. Information will be collected at baseline and at 12 month follow-up and refers to the funding and organisational features of the care home; the number and overall demographic and health characteristics of residents; the number and oral health training of the staff; the provision of oral health programmes; and the arrangements for health care of the residents.

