#### COVID-19

The coronavirus (COVID-19) pandemic has impacted excessively on care homes and raises many challenges for their safe operation and protection of the residents and staff. To ensure residents, staff and the research team are protected every precaution will be taken to minimise the risk of infection. Face-to-face visits will only be undertaken where care homes have been COVID-free for at least 14 days. Prior to each face-to-face visit, care homes will be asked to complete a COVID-19 screening questionnaire to assess and minimise any risk. Researchers will also provide a declaration of their own COVID status (no symptoms or contact with known COVID cases for 14 days). During each visit, researchers will wear a face mask, ensure social distancing and perform hand washing/hand sanitization.

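### At 12 months the wording lets a staff mouth inspection, done in the intervention arm only, come just before blinded plaque scoring; the examiner should score first

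*Protocol article*

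**What the plan says.** All references are to the protocol article.

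- **Staff OHAT.** Under Intervention description, one component is "Administration by trained care home staff of OHAT, a brief and practical assessment of the resident’s oral health needs". Its timing is given in one sentence: "Administration will take place immediately prior to the initial dental assessment at baseline and at the 12-month follow-up visit". Staff then complete or update a Personal Oral Care Plan. No cleaning step is attached to the OHAT.
- **One arm only.** Completion of the staff OHAT is a fidelity item, and of the fidelity data the Outcomes section says: "This refers only to the care homes in the intervention arm of the study". For the comparator, "Participants on the control arm will receive routine practice".
- **Plaque scoring.** Clinical outcomes include "the proportion of teeth with visible plaque and the proportion of teeth that bleed on probing". In the data collection plans, "The dental examination will be undertaken at baseline and at 12 months by trained dental examiners". The examiner also completes a separate OHAT in both arms: "The dental examiner will undertake this assessment at baseline and 12 months".
- **Blinding.** Under Who will be blinded, care homes and residents are unblinded, the dental examiners are to be blinded, and staff are told not to disclose allocation to them.
- **Use of the result.** There is no primary outcome. The study is meant to help choose one and to supply effect estimates for the definitive trial. Arm differences are reported with 95% confidence intervals.

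**The concern.** Visible plaque is the listed clinical outcome that recent cleaning can change most directly. At the visit where it is scored, unblinded carers in intervention homes look into each participant's mouth for study purposes, and carers in control homes do not. Those same carers brush residents' teeth, assist them or remind them. If the inspection comes first, a carer who sees plaque has an occasion to deal with it before the examiner arrives. Blinding the examiner does not guard against this, because the examiner scores what is then in the mouth.

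A second route is loss of blinding. A staff OHAT done just before or beside the examination is a visible step that exists only in intervention homes, so its presence can disclose the allocation.

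Either route could tilt the 12-month plaque contrast towards the intervention. That contrast is one of the inputs to choosing the definitive trial's outcome and its assumed effect.

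**Working it through.** The plan gives no figure on this point, so there is none to reproduce. The check is a comparison of the text, followed by an illustration on assumed values.

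**Step 1: readings of the timing sentence.**

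| Reading | Baseline | 12 months |
|---|---|---|
| The adverbial phrase governs both time points | staff OHAT, then examiner | staff OHAT, then examiner |
| It governs baseline only | staff OHAT, then examiner | staff OHAT at the same visit, order not set |

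The first reading requires the unfavourable order at 12 months. The second permits it, and equally permits the examiner to go first. Neither secures examiner-first.

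**Step 2: is the step confined to one arm?** Yes. The staff OHAT is an intervention component, its completion is tracked only in intervention homes, and controls continue routine practice. The OHAT that both arms share is the examiner's own.

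**Step 3: what counts as artefact?** The regime includes assisted brushing each morning and evening. A mouth that is cleaner because of that morning's brushing shows the allocated treatment at work. Only extra cleaning prompted by the inspection, before scoring, is artefact.

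**Step 4: could the listed data show it?** The article lists no item on time since last brushing. The Weekly Oral Hygiene Record logs daily brushing, but is listed for intervention homes only, so it cannot support a comparison between arms.

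**Step 5: illustration (assumptions, not trial data).** Let *f* be the share of intervention residents who get an extra, inspection-prompted clean before scoring. Let *r* be the resulting fall in the percentage of teeth with visible plaque, in percentage points. With no such clean in controls:

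shift in the arm difference = *f* × *r*

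| *f* | *r* = 10 points | *r* = 30 points |
|---|---|---|
| 0 | 0 | 0 |
| 0.25 | 0.25 × 10 = 2.5 | 0.25 × 30 = 7.5 |
| 0.5 | 0.5 × 10 = 5 | 0.5 × 30 = 15 |
| 1 | 1 × 10 = 10 | 1 × 30 = 30 |

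The documents do not say where in this table the trial would fall. The more plaque the morning brushing has already removed, the smaller *r* must be.

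**The case against.** The case against is substantial, and most of it limits the point.

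- **Cleaning is an inference.** The OHAT is described as an assessment, and the stated follow-on is updating a care plan. This stands: the documents show an opportunity, not an event. If the inspection really is immediately before scoring, there is also little time to brush in between.
- **Same-day brushing is the treatment.** A reader might infer that the plaque contrast would reflect same-day cleaning instead of a year of daily care. The documents do not support that, since morning brushing is part of the allocated regime.
- **Advance notice is not one-sided.** A reader might infer that announced visits favour the intervention. The COVID-19 section says "Prior to each face-to-face visit, care homes will be asked to complete a COVID-19 screening questionnaire", and this applies to homes in both arms. Tidying up in control homes is equally possible and would shrink the contrast.
- **Adjustment for time since brushing is unsound as a remedy.** It is a post-randomisation variable that the intervention targets, so adjusting for it can remove real effect. This stands and shapes the fix.
- **Limited consequence.** There is no primary outcome, plaque is one of several measures, and one brushing does not change tooth counts or caries. Outcome choice also draws on missing-data rates and stakeholder interviews. This stands.
- **An article may leave visit order to the full protocol or an examiner manual.** This stands only in part. Those documents may settle the order, but the article does state a timing rule for this step, and that rule is ambiguous or unfavourable at the outcome visit.

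**Conclusion.** The point holds as a low-cost improvement. The plan places an unblinded, intervention-arm-only mouth inspection at the visit where visible plaque is scored. Its wording allows that inspection to come immediately before the scoring, and on one reading requires it. An arm-specific prompt to clean, or disclosure of allocation to the examiner, therefore cannot be ruled out.

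The size is unknown and may be zero. The illustrative shifts, from 0 to 30 percentage points, rest entirely on assumed shares and plaque reductions and are not an estimate for this trial. The point concerns mainly visible plaque. Its consequence is confined to how the plaque contrast is used in choosing the outcome and effect size for the definitive trial.

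The blinding argument rests on the section Who will be blinded. The section on unblinding procedure describes only the statistician as blinded, and that difference needs reconciling in its own right.

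**What to change.** In Intervention description, replace the single timing sentence with one that treats the two visits separately. For 12 months, state that the dental examiner's assessment is completed first. The staff OHAT then follows, out of the examiner's sight and without access to the examiner's scores, or is done on another day.

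Add one CRF item, recorded by the research assistant for every participant in both arms at baseline and 12 months: time of last tooth brushing. Report it descriptively by arm. Do not present a plaque difference adjusted for it as the effect estimate.

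The cost is slightly tighter coordination of the visit and one extra CRF item. Implementation runs from baseline to the 12-month time point, so reordering the closing visit takes nothing from the year of care, and completion of the staff OHAT can still be recorded as a fidelity measure. If the full protocol or an examiner manual already fixes this order, the article's sentence needs only to be brought into line with it.

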
### Criteria for discontinuing or modifying allocated interventions

It is not expected that the oral health intervention described above will cause any adverse effects. Participants and care homes are free to withdraw from the study at any point in time. Given the co-design process undertaken prior to the feasibility study, there will be no modification of allocated treatments. However, a parallel process evaluation guided by Pfadenhauer et al.’s framework [21] will be undertaken to refine the intervention ahead of a definitive trial.

### Strategies to improve adherence to interventions

There will be no additional strategies to improve the adherence to the intervention. Adherence to the intervention will be monitored by collecting information on completion rates (fully, partially or not completed) for the following: (1) OHAT administered by trained care staff to participants, (2) Personal Care Plan for participants, (3) Weekly Oral Hygiene Record of participants, and (4) Care Staff Completed Training.

### Relevant concomitant care permitted or prohibited during the trial

In order to be pragmatic, the intervention will be delivered alongside any oral care practices currently in place in the care homes and being provided to residents. Care homes will not be asked to cease any practices that they are currently undertaking on either control or intervention arm. Existing care home practices will be recorded and reported as a part of the feasibility study.

### Provisions for post-trial care

Harm suffered by participants from trial participation is not anticipated. In the event of complaints and concerns, these can be directed towards the research team, and participants will have the relevant contact details.

Care homes in the intervention arm will be informed that they can retain the training package and intervention materials after the end of the feasibility study. The intervention training package and materials will also be made available to the control arm care homes after the end of the study.

### Outcomes

This study does not have a primary outcome measure. The main aim of this study is to determine the feasibility of a multi-centre cluster-randomised trial for the prevention of oral disease in older people in care homes. The feasibility study will provide necessary information to enable selection of the most appropriate primary outcome measure, estimates of treatment effects and other important parameters to plan for a definitive trial. The outcome measures that will be recorded in this study are as follows:
Clinical outcomes (assessed at baseline and 12 months by a dental examiner) will include the number of teeth, number of teeth with coronal and root caries lesions, the proportion of teeth with visible plaque and the proportion of teeth that bleed on probing;Oral symptoms and urgent dental care refers to the number of reported episodes of dental pain, sepsis, discomfort and urgent dental care appointments (collected weekly by care home staff and at baseline, 6 and 12 months by researchers);Health-related quality of life using the EuroQol five dimensions questionnaire – EQ-5D5L [27] (collected at baseline, 6 and 12 months);Oral health-related quality of life using the Oral Impacts on Daily Performances (OIDP) [28] (collected at baseline, 6 and 12 months); andOral health needs assessed by OHAT [26] (collected by dental examiners at baseline and 12 months).

The EQ-5D is the most commonly used outcome in health economics evaluation studies to calculate QALYs, preferred also by NICE [29]. Its responsiveness has not been proven for oral conditions and therefore the additional use of condition-specific measures is recommended [30]. The OIDP is a brief and widely used oral health-related quality of life outcome measure, validated also amongst older adults in the UK [28]. It is included in the national dental health surveys of adults in the UK [31] and previously used in care homes in London in an interviewer-administered format to provide self-reports of residents about the impact of oral conditions on key aspects of their daily life, such as eating, speaking, cleaning teeth, smiling, relaxing, and enjoying the contact of other people [2].

Data will be collected to facilitate the assessment of the fidelity of the intervention. This refers only to the care homes in the intervention arm of the study and will include information on completion rates (fully, partially or not completed) for the following: (1) OHAT administered by trained care staff to participants; (2) Personal Care Plan for participants; (3) Weekly Oral Hygiene Record of participants; (4) Care Staff Completed Training.

As part of the process evaluation, semi-structured interviews with care home staff (managers, carers and other staff) and residents will assess the intervention’s feasibility (issues relating to recruitment, retention and fidelity) and acceptability. How the intervention could be embedded in standard practice will also be explored using the different domains of Pfadenhauer et al.’s [21] framework (Table 1). Specifically, the framework will be used to determine the factors that are important for implementation.

**Table 1 Tab1:** Domains and questions for reflection from Pfadenhauer et al. [21]

Main	Questions for reflection
Intervention characteristics	Which intervention characteristics interact with the setting, the context and the implementation? How do these intervention characteristics interact with the setting, the context and the implementation?
Context	How do aspects of the context interact with the intervention? Which aspects of the context interact with the implementation of the intervention?
Implementation theory	Which theoretical underpinning guides the implementation? How does this theory interact with the setting and the context? How does it interact with the intervention?
Implementation process	Which stages of the implementation process are passed through during implementation? How does the implementation process interact with the setting and the context? How does it interact with the intervention?
Implementation strategy	Which strategies are employed during implementation? How do these implementation strategies interact with the setting and the context? How do they interact with the intervention?
Implementation agents	Which agents are involved in the implementation effort? How do these implementation agents interact with the setting and context? How do they interact with the intervention?
Implementation outcomes	Which implementation outcomes are reported with the setting and the context? How do these implementation outcomes interact with the intervention outcomes?
Setting	Which aspects of the setting interact with the intervention? How does the setting interact with the intervention? How does it interact with the context? How does it interact with implementation?

Additional semi-structured interviews with key stakeholders (care home staff and residents, family members and policymakers) will help identify a core set of relevant outcomes, and will also explore issues associated with the valid, reliable and efficient collection and reporting of a core outcome set. During the interview, stakeholders will be presented with information on a range of costs, outcomes and cost per outcome. They will be asked to consider how important these costs and outcomes are and why. A cost-consequence model to inform a future larger scale definitive trial will be produced.

